## Abstract

**Background:**

A recent study shows that a multifaceted strategy using an individualised intra-abdominal pressure titration strategy during colorectal laparoscopic surgery results in an acceptable workspace at low intra-abdominal pressure in most patients. The multifaceted strategy, focused on lower to individualised intra-abdominal pressures, includes prestretching the abdominal wall during initial insufflation, deep neuromuscular blockade, low tidal volume ventilation settings and a modified lithotomy position. The study presented here tests the hypothesis that this strategy improves outcomes of patients scheduled for colorectal laparoscopic surgery.

**Methods:**

The Individualized Pneumoperitoneum Pressure in Colorectal Laparoscopic Surgery versus Standard Therapy (IPPCollapse-II) study is a multicentre, two-arm, parallel-group, single-blinded randomised 1:1 clinical study that runs in four academic hospitals in Spain. Patients scheduled for colorectal laparoscopic surgery with American Society of Anesthesiologists classification I to III who are aged > 18 years and are without cognitive deficits are randomised to an individualised pneumoperitoneum pressure strategy (the intervention group) or to a conventional pneumoperitoneum pressure strategy (the control group). The primary outcome is recovery assessed with the Post-operative Quality of Recovery Scale (PQRS) at postoperative day 1. Secondary outcomes include PQRS score in the post anaesthesia care unit and at postoperative day 3, postoperative complications until postoperative day 28, hospital length of stay and process-related outcomes.

**Discussion:**

The IPPCollapse-II study will be the first randomised clinical study that assesses the impact of an individualised pneumoperitoneum pressure strategy focused on working with the lowest intra-abdominal pressure during colorectal laparoscopic surgery on relevant patient-centred outcomes. The results of this large study, to be disseminated through conference presentations and publications in international peer-reviewed journals, are of ultimate importance for optimising the care and safety of laparoscopic abdominal surgery. Selection of patient-reported outcomes as the primary outcome of this study facilitates the translation into clinical practice. Access to source data will be made available through anonymised datasets upon request and after agreement of the Steering Committee of the IPPCollapse-II study.

**Trial registration:**

ClinicalTrials.gov, NCT02773173. Registered on 16 May 2016. EudraCT, 2016-001693-15. Registered on 8 August 2016.

**Electronic supplementary material:**

The online version of this article (10.1186/s13063-019-3255-1) contains supplementary material, which is available to authorized users.

## Background

Compared to open surgery, laparoscopic surgery generally results in better outcomes [1, 2]. Compared to open abdominal surgery, a laparoscopic approach during abdominal surgery is associated with less blood loss and fewer needs for blood transfusions [3, 4], faster recovery of bowel function and oral intake resumption [5, 6], fewer analgesic requirements [6, 7] and a shorter length of hospital stay (LOS) [3–8]. Patient-reported outcomes (PROs) are new tools for testing quality of recovery in the postoperative setting, and the Post-operative Quality of Recovery Scale (PQRS) has been successfully tested in previous studies.

A high intraoperative intra-abdominal pressure (IAP) is clearly associated with perioperative morbidity [9–14]. While guidelines for laparoscopic abdominal surgery recommend the lowest possible IAP at which the surgeon has adequate workspace rather than using a predetermined level [15, 16], it remains common practice to use a standard IAP level throughout the surgical procedure, usually between 12 and 15 mmHg and sometimes even higher depending on surgical indication [17]. Interestingly, while the surgical condition depends mainly on the intra-abdominal volume (IAV) and the workspace obtained at a given IAP, the focus during pneumoperitoneum insufflation remains with the applied IAP [18].

Several factors improve the relation between IAP and the obtained surgical workspace, including patient positioning [19], use of neuromuscular blockade [20, 21] and prestretching of the abdominal wall [22]. The previous pivotal and feasibility study, Individualized Pneumoperitoneum Pressure in Colorectal Laparoscopic Surgery I (IPPCollapse-I), showed that combining all these factors with individualised IAP titration resulted in an acceptable workspace at 8 mmHg IAP in 61 out of 78 patients (78%) [23]. The IPPCollapse-II study presented here tests the hypothesis that this individualised pneumoperitoneum pressure strategy improves recovery of PQRS score when compared to a conventional strategy that uses a fixed pneumoperitoneum pressure approach in patients undergoing scheduled colorectal laparoscopic surgical intervention.

## Methods/design

### Study reporting

This report follows the Standard Protocol Items: Recommendations for Interventional Trials and Patient-Reported Outcomes (SPIRIT-PRO) guidelines [24, 25]. Additional file 1 details the IPPCollapse-II SPIRIT checklist.

### Study design

The IPPCollapse-II study is a multicentre, two-arm, parallel-group, single-blinded randomised clinical study. The enrolment and assesments during the study period are shown in Fig. 1. The study flowchart is shown in Fig. 2.

**Fig. 1 Fig1:**
[figure not shown]
Study timepoints

**Fig. 2 Fig2:**
[figure not shown]
IPPCollapse II flowchart

### Study setting

The IPPCollapse-II study runs in the operating room and surgical wards of four academic hospitals in Spain (detailed in Additional file 2).

### Study population

Patients are eligible for participation if they (1) are scheduled for laparoscopic colorectal surgery, (2) are aged > 18 years, (3) have an American Society of Anesthesiologists (ASA) physical status I to III, and (d) have no cognitive deficits. Exclusion criteria are (1) no written informed consent; (2) emergency or unplanned surgery; (3) pregnancy or breastfeeding; (4) immunologic or neuromuscular diseases; (5) advanced stage of cardiopulmonary, renal or hepatic disease; and (6) allergy to or contraindications for rocuronium or sugammadex.

### Randomisation and blinding

Patients are randomised in a 1:1 ratio to an individualised pneumoperitoneum pressure strategy (the intervention group) or a standard pneumoperitoneum pressure strategy (the control group). Local investigators perform randomisation using a web-based automated randomisation system (Biostatistics Unit of the Health Research Institute La Fe, Valencia, Spain). Randomisation is performed with random block sizes and is stratified per centre. While attending anaesthesiologists are aware of the assigned pneumoperitoneum pressure strategy, the attending surgeons as well as the patients remain unaware of the assigned pneumoperitoneum pressure strategy at all times, i.e. before surgery, during surgery and after surgery. The PQRS is a patient-reported outcome (PRO), meaning that the investigator has little room to cause bias. The pneumoperitoneum insufflator screen is covered by a surgical drape. Study team members, who are not blinded to randomisation, perform postoperative PQRS measurements.

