### Primary outcome

The primary outcome is the recovery of the PQRS at postoperative day 1 (POD1) (see the subsequent sections for details).

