### Post-operative Quality of Recovery Scale

The PQRS is a validated multidimensional PRO tool [29–31] designed to assess patients’ recovery to baseline status in the postoperative period (www.postopqrs.com). In every patient a baseline measurement of PQRS is performed prior to surgery. After surgery, the measurement of the PQRS is repeated at 15 min (T15) and at 40 min (T40) after arrival in the PACU, as well as in the ward on the morning of POD1 and POD3. The PQRS is a verbal survey tool that depicts recovery in the following five domains: physiologic, nociceptive, emotive, functional, cognitive, and also collects overall patient perspective. Each of these domains is assessed with multiple items on an ordinal scale and compared with baseline to evaluate recovery (see Table 2 for details). Recovery is a dichotomised outcome defined by a return to at least baseline values or better at each of the postoperative measurement time points. Overall recovery requires recovery in all domains being assessed, and failure in any domain results in failure of overall recovery.

**Table 2 Tab2:** Post-operative Quality of Recovery Scale (PQRS)

Domain	Variable	Score	Baseline	T15	T40	POD1	POD3
Physiologic	Blood pressure	1–3	+	+	+	+	+
Physiologic	Heart rate	1–3	+	+	+	+	+
Physiologic	Temperature	1–3	+	+	+	+	+
Physiologic	Respiration	1–3	+	+	+	+	+
Physiologic	SpO2	1–3	+	+	+	+	+
Physiologic	Airway	1–3	+	+	+	+	+
Physiologic	Agitation	1–3	+	+	+	+	+
Physiologic	Consciousness	1–3	+	+	+	+	+
Physiologic	Activity on command	1–3	+	+	+	+	+
Nociceptive	Pain	1–5 Likert	+	+	+	+	+
Nociceptive	PONV	1–5 Likert	+	+	+	+	+
Emotional	Sadness/depression	1–5 Likert	+	+	+	+	+
Emotional	Anxiety/nervousness	1–5 Likert	+	+	+	+	+
Functional	Stand	1–3	+	–	–	+	+
Functional	Walk	1–3	+	–	–	+	+
Functional	Eat/drink	1–3	+	–	–	+	+
Functional	Get dressed	1–3	+	–	–	+	+
Cognitive	Name, city and DOB	TF 0	+	–	–	+	+
Cognitive	Numbers forward	TF 2	+	–	–	+	+
Cognitive	Numbers backwards	TF 1	+	–	–	+	+
Cognitive	Word task: list	TF 3	+	–	–	+	+
Cognitive	Executive memory	TF 3	+	–	–	+	+
Overall patient perspective	Ability to work	1–5	–	–	–	–	+
Overall patient perspective	Ability to perform ADLs	1–5	–	–	–	–	+
Overall patient perspective	Clarity of thought	1–5	–	–	–	–	+
Overall patient perspective	Satisfaction anaesthesia care	1–5	–	–	–	–	+

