This study has limitations. We exclude ASA IV patients, who could benefit more from working with low IAP. Since we test a multifaceted strategy, it will remain uncertain which part of the strategy will have the largest impact. In fact, it could very well be that not all parts have the same magnitude of effect, and it is even possible that some parts have negligible  effects. Of note, reversal of neuromuscular blockade with sugammadex instead of neostigmine could improve PQRS recovery at T40 although not at POD1 or POD3. Surgeons, blinded for the actual IAP, will evaluate surgical conditions in a practical dichotomous manner as adequate or not, depending on whether any corrective action is needed. This way of measurement might make comparisons with other studies difficult, such as those using the Leiden-Surgical Rating Scale. The anaesthesiologists collecting the PQRS evaluations are not blinded for the assigned strategy, as they were present during the surgical procedure. However, the risk of bias will be very low, as the PQRS is a ‘patient-reported’ outcome, and the patients remain blinded at all times, including the time at which the PQRS score is collected. We calculated the sample size of our study on PQRS differences; thus, our sample could be underpowered for some secondary outcome that can potentially require a larger sample. In conclusion, the IPPCollapse-II study is designed to test if an individualised pneumoperitoneum pressure and optimised management versus conventional care will affect the outcome of patients undergoing colorectal laparoscopic surgery using relevant patient-centred outcomes.

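### The patient-reported label does not justify calling assessor bias very low: 14 of the 22 PQRS items at POD1 are physiologic observations or cognitive tests, collected by unblinded staff who attended the operation

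*Protocol article*

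**What the plan says.** Under Randomisation and blinding the protocol article states "Study team members, who are not blinded to randomisation, perform postoperative PQRS measurements". The Discussion adds who they are: "The anaesthesiologists collecting the PQRS evaluations are not blinded for the assigned strategy, as they were present during the surgical procedure".

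Both places then set the risk aside. The methods section reasons that "The PQRS is a patient-reported outcome (PRO), meaning that the investigator has little room to cause bias". The Discussion says "However, the risk of bias will be very low, as the PQRS is a ‘patient-reported’ outcome, and the patients remain blinded at all times".

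The section on the scale describes something broader than self-report: "The PQRS is a verbal survey tool that depicts recovery in the following five domains: physiologic, nociceptive, emotive, functional, cognitive". Table 2 lists the items by domain and time point. The same section makes overall recovery all-or-nothing across domains. The Analysis plan bases the sample size on an odds ratio of 2.65 for recovery in the physiologic domain, with 170 evaluable patients.

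**The concern.** An unblinded assessor is tolerable when the patient, who does not know the allocation, supplies the answer and the assessor only records it. The protocol relies on exactly that argument. It works for pain, nausea and mood. It does not work for an observation such as "Activity on command", or for a digit-span or word-list test, where the assessor observes, prompts or scores.

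The primary outcome mixes both kinds of item, and the assessor knows the arm. Any leniency or severity linked to the arm would therefore enter the primary comparison. A reader of the results would have been told that this risk is negligible, on a ground that covers only part of the scale.

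**Working it through.** **1. Item count at POD1 (Table 2, protocol article).** The protocol gives no count of its own to reproduce.

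| Domain | Items at POD1 | Nature |
|---|---|---|
| Physiologic | 9 | observed or measured |
| Nociceptive | 2 | self-rated, faces scale |
| Emotional | 2 | self-rated, faces scale |
| Functional | 4 | graded by ease; taken here as self-reported |
| Cognitive | 5 | performance tests with a tolerance factor |
| Overall patient perspective | 0 | collected at POD3 only |

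Total: 9 + 2 + 2 + 4 + 5 + 0 = 22. Not patient-reported: 9 + 5 = 14, and 14/22 = 64%.

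**2. Items that leave room for judgement.** Blood pressure, heart rate, temperature and SpO2 are probably instrument readings. Removing them gives 14 − 4 = 10 of 22: respiration, airway, agitation, consciousness, activity on command and the five cognitive tests. That an examiner scores the cognitive tests is inferred from the verbal format and the tolerance factor; the article does not say so outright.

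**3. Route to the primary outcome.** Each domain can fail a patient by itself, so a physiologic or cognitive rating can turn a recovered patient into a non-recovered one. The reverse is more limited. Lenient rating creates an overall recovery only if the nociceptive, emotive and functional domains have all recovered too. If the endpoint is the physiologic domain alone, as the sample size paragraph implies, that limit disappears.

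**4. Illustration of size.** The inputs are 170/2 = 85 per arm (Analysis plan), a two-sided 5% test and no true effect. Two inputs are assumptions, because the article gives neither: the true recovery proportion p, and the share m of intervention-arm non-recoverers who are scored as recovered. A simple two-proportion test stands in for the planned ordinal model.

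The apparent proportions are p in the control arm and p + m(1 − p) in the intervention arm. The chance of significance favouring the intervention is about Φ(d/SE − 1.96), with d = m(1 − p).

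Worked case, p = 0.20 and m = 0.05:
- d = 0.05 × 0.80 = 0.04, so 0.20 is compared with 0.24.
- SE = √(0.20 × 0.80/85 + 0.24 × 0.76/85) = 0.0635.
- d/SE = 0.63, and Φ(0.63 − 1.96) = Φ(−1.33) ≈ 9%.

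Exact binomial summation gives:

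| Assumed recovery p | m = 5% | m = 10% |
|---|---|---|
| 20% | 9.4% | 23.3% |
| 30% | 7.0% | 15.7% |
| 40% | about 6% | 12.5% |
| 70% | 4.1% | 6.4% |
| 85% | 3.4% | 4.6% |

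The nominal value in that direction is 2.5%.

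**5. What m means under the all-domain rule.** If only a share q of non-recoverers have all self-rated domains recovered, the upgrade rate needed among them is m/q. With m = 5%, an assumed q of 50% needs 0.05/0.50 = 10%, and q of 25% needs 0.05/0.25 = 20%. The table is therefore easier to reach for a physiologic-only endpoint than for overall recovery.

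**The case against.** **Disclosure.** The trial is labelled single-blinded, and the Discussion lists unblinded collection as a limitation. That stands: nothing is concealed. But the disclosure is cancelled by the same incomplete reason, so the justification still needs correcting.

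**Item share.** A reader might infer that 64% measures how exposed the outcome is. It does not. Recovery is counted by domain, four of the 14 items are probably device readings, and the items are not equally open to influence.

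**Power of the 14 items.** A reader might infer that these items alone can produce a recovery. They can cause a failure alone. To produce an overall recovery they also need the three self-rated domains to have recovered. Harsher scoring of controls is not limited in this way, but the illustration does not model it.

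**Actual bias.** A reader might infer that the primary result will be biased by the amounts shown. The documents give no recovery rate and no evidence of differential scoring. They support a risk of unknown size, and at high recovery the illustrated effect is small.

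**Surgeons.** The methods say "the attending surgeons as well as the patients remain unaware of the assigned pneumoperitoneum pressure strategy at all times". Table 1 lists the modified leg position and the stepwise pressure reduction for the intervention arm only, so a reader might infer that surgeons can identify the arm. That is plausible but not established. Leg position in the control arm is not described, surgeons do not collect the PQRS, and the Definitions and Discussion sections already make the narrower claim that surgeons are blinded to the pressure. This is a wording matter, separate from the main point.

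**Conclusion.** The point holds as a faulty justification for a fixed design choice. The patient-reported argument, together with patient blinding, covers the nociceptive, emotive and functional items (8 of 22 at POD1). It does not cover the physiologic and cognitive domains (14 of 22, about 10 open to judgement or prompting), and the physiologic domain is the one on which the trial is sized. The claim of very low bias for the outcome as a whole is therefore unsupported.

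The size is unknown. With an assumed recovery of 20–40% and an assumed 5% upgrade, the one-direction false-positive chance goes from 2.5% to about 6–9%; at 70–85% recovery it is about 3–4%. These figures illustrate sensitivity and do not estimate bias in this trial. The change should be made, but the point does not show that the primary result is invalid.

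**What to change.** 1. **Wording.** Replace the two reassuring statements (Randomisation and blinding; Discussion) with one that limits the patient-reported argument to the nociceptive, emotive and functional domains and names assessor bias as a risk for the physiologic and cognitive domains. This costs only an edit.
2. **Sensitivity analysis.** Before any unblinded analysis, prespecify POD1 recovery on the nociceptive, emotive and functional domains alone. This is one extra analysis on data already collected. It leaves out the domain behind the sample size, so a difference from the main result could be a real domain-specific effect as well as scoring bias. It should be read as supportive. The self-rated items are still asked verbally by the same staff, so they are better protected but not immune.
3. **Assessors, only for patients still to be enrolled.** Have the POD1 and POD3 PQRS done by an existing team member who did not attend that operation and cannot see the allocation. The cost is some scheduling burden. Recruitment was expected to finish in October–November 2018, so this may reach few patients or none; items 1 and 2 remain possible either way.
4. **Minor.** Align the methods sentence on surgeons with the narrower description in the Definitions and Discussion sections, namely that they are blinded to the pressure itself.

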### Standard pneumoperitoneum pressure strategy

The standard strategy consists of the following elements, to be performed in the same order in all patients in the control group: (1) patients are placed in a position according to the surgeon’s preference within a predefined range of Trendelenburg position (0–30°); (2) patients receive moderate neuromuscular blockade with rocuronium, cisatracurium or atracurium throughout surgery to maintain a train of four (TOF) between 2 and 4; and (3) the IAP is set at 12 mmHg throughout surgery. At any time, surgeons can request an IAP increase if the workspace becomes ‘inadequate’; in that case, the IAP is increased in steps of 1 mmHg during 1-min intervals to a maximum of 15 mmHg, but not higher than the level at which the surgical workspace returns to ‘adequate’. Surgeons will be warned if the IAP reaches the predefined upper limit.

Neuromuscular blockade pharmacological reversion is achieved with neostigmine (2.5 mg or 30–50 μg∙kg^− 1^), according to usual care.

### Individualised pneumoperitoneum pressure strategy

The multifaceted individualised pneumoperitoneum strategy consists of the following elements, which will be performed in the same order in all patients in the intervention group: (1) patient position is modified to increase the anteroposterior intra-abdominal space by correcting lumbar lordosis; (2) patients receive deep neuromuscular blockade throughout surgery to maintain a TOF of 0 and a post-tetanic count (PTC) between 1 and 5; (3) the abdominal wall and muscles are prestretched by maintaining an IAP of 15 mmHg for 5 min during the first CO_2_ gas insufflation and insertion of trocars (to achieve this, the CO_2_ gas insufflator will be initially set at 15 mmHg with a flow rate of 3 L∙min^− 1^); and (4) individualised IAP titration is used when the patient is placed in the surgical position (0–30° Trendelenburg); for this, the flow rate is increased to 30 L∙min^− 1^ and the IAP is decreased from 15 to 12 mmHg, and thereafter stepwise to 11, 10, 9 and finally 8 mmHg as long as the attending surgeon keeps an ‘adequate’ workspace. As in the standard pneumoperitoneum pressure group, surgeons can request an IAP increase up to 15 mmHg, which will be performed likewise. Of note, a pressure increment can be requested by the surgeon at all times in both study arms, where it always follows a similar approach; the previous feasibility study showed that an IAP increase was requested only one time in one-fifth of the patients and never twice [23].

Neuromuscular blockade pharmacological reversion at the end of surgery, before tracheal extubation, is achieved with sugammadex 4 mg∙kg^− 1^.

For clarity, the elements of the two group strategies are summarised in Table 1.

**Table 1 Tab1:** Intervention sequence

Standard pneumoperitoneum pressure strategy (SPP group)	Individualised pneumoperitoneum pressure strategy (IPP group)
1. Trendelenburg (0–30°) placement	1. Trendelenburg (0–30°) + ‘modified lithotomy position’, with flexed hips (between 45 and 90°) and legs raised in padded supports to increase anteroposterior intra-abdominal space
2. Moderate neuromuscular blockade throughout surgery (TOF between 2 and 4)	2. Deep neuromuscular blockade throughout surgery (TOF of 0 and a PTC between 1 and 5)
3. No prestretching of abdominal wall muscles	3. Prestretching of abdominal wall muscles by maintaining an IAP of 15 mmHg for 5 min during the first CO_2_ gas insufflation and insertion of trocars (flow rate at 3 L∙min^− 1^)
4. IAP is set at 12 mmHg throughout surgery	4. IAP down-titration (flow rate at 30 L∙min^− 1^) from 15 to 12 mmHg, and thereafter stepwise to 11, 10, 9 and finally 8 mmHg as long as ‘adequate’ workspace is preserved (by surgeon’s judgement)
5. Surgeons can request an IAP increase if workspace becomes ‘inadequate. IAP is increased in steps of 1 mmHg during 1-min intervals to a maximum of 15 mmHg. Surgeons are warned when upper limit is reached	5. Surgeons can request an IAP increase if workspace becomes ‘inadequate’; IAP is increased in steps of 1 mmHg during 1-min intervals to a maximum of 15 mmHg. Surgeons are warned when upper limit is reached

*TOF* train of four, *IAP* intra-abdominal pressure, *PTC* post-tetanic count

